## Methods

### Study aims

The primary aim of this study is to compare the effectiveness of in-person START practices versus START telemental health using a randomized control, non-inferiority design. It is hypothesized that telemental health START will not be inferior to in-person START in the reduction of emergency psychiatric service use, time-to-discharge, improvement in mental health stability and perceived quality of care. This finding will support the use of telemental health practices as a valuable alternative to in-person care.

A secondary aim of this study is to evaluate heterogeneity of treatment response by assessing differences in outcomes across diverse groups, including race, ethnicity, language spoken, rural settings, and level of intellectual disability. It is hypothesized that telemental health will not be inferior to the in-person condition across diverse groups, except for those living in rural settings. We hypothesize improved perceived quality of care will be found among those in the telemental health condition who live in a rural setting, compared to those living in a rural setting who are in the in-person condition, given the known difficulty in accessing in-person services for those living far from care. This finding will support equitable effects of telemental health START practices among diverse racial/ethnic and developmental groups, with potential added value for those living in rural settings.

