### Non-inferiority design

This study will employ a non-inferiority design. Non-inferiority trials permit a ‘new’ treatment to be considered efficacious if treatment effects fall within a pre-specified margin (the non-inferiority [NI] margin) of the effects identified in the reference treatment [27]. In this study, the ‘new treatment’ will be the telemental health condition, while the in-person condition will serve as the ‘established/reference treatment’. The merits of telemental health that justify consideration as an alternative to the standard of care include increased accessibility and lower cost. The merits of telemental health are assumed to be valuable enough that, even if effects fall slightly short of the reference treatment by a clinically tolerable amount, it is a viable alternative to the standard of care when circumstances would indicate its use [28].

The NI margin has been set for the FEIS, given its primacy in outcome. A 7-point change in the total FEIS score, which is equivalent to a standardized delta of 0.5, will identify the lower threshold for clinically meaningful difference [21]. Thus, a 99% confidence interval for the slope for the group assignment variable will be constructed and its lower limit will be compared to the − 7.0 non-inferiority margin. The 99% confidence interval, reflecting the α cutoff of 0.008, was selected to account for multiple comparisons, which will be determined post-hoc via the Benjamini Hotchberg procedure [29]. The non-inferiority margin for emergency service use will be a 38% reduction in the probability of a START crisis contact between START in-person and START telemental health. Last, we have identified a five-point change in the ABC irritability subscale as the non-inferiority margin. This study was registered on April 20th, 2022 on clinicaltrials.gov (NCT05336955; https://clinicaltrials.gov/ct2/show/NCT05336955 ).

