### Statistical analyses

The efficacy analyses will be conducted as both intention-to- treat (ITT; “as allocated”) and per protocol (PP; “as-treated”) since ITT can bias towards the null, leading to false claims of non-inferiority, and PP can fail to preserve the balance inherent to randomization (30, 31). For the analysis, the first step will be to examine demographic and clinical characteristics across study conditions to assess that the randomization worked as expected. If significant sociodemographic differences emerge, these variables will be included in the multivariate analyses since baseline adjustment has been shown to increase precision in randomized control trials (32). All analyses, for the factorial design, will be examined using a series of multilevel (or “mixed” effects) general linear regression models that account for clustering (via a random intercept) across sites. For these models, the independent variable of interest will be telemental health versus in-person START. The dependent variables will be calculated as change scores/differences since baseline. Two-way (Intervention group x time) interaction terms will test the primary study aim. Three-way (Intervention group x demographic population x time) interaction terms will test the secondary study aim. Effect sizes will be calculated using Cohen’s *d*. To accommodate increased false discovery rate, the study will adjust the significance threshold using the Benjamini-Hochberg procedure. This procedure is conducted after all tests are concluded; α = .01 will be assumed for the power analysis.

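### The three-way interaction suits the heterogeneity aim, but alone it cannot establish the two hypotheses stated under that aim: non-inferiority across groups and better perceived care among rural participants

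*Protocol article*

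**What the plan says.** In the protocol article, Study aims opens the secondary aim as a heterogeneity question: "A secondary aim of this study is to evaluate heterogeneity of treatment response by assessing differences in outcomes across diverse groups". Two directional hypotheses follow. The first is "It is hypothesized that telemental health will not be inferior to the in-person condition across diverse groups, except for those living in rural settings". The second concerns one outcome and one group: "We hypothesize improved perceived quality of care will be found among those in the telemental health condition who live in a rural setting", the comparator being rural participants in the in-person arm. The section then says what would follow: "This finding will support equitable effects of telemental health START practices among diverse racial/ethnic and developmental groups".

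Statistical analyses gives the test for this aim: "Three-way (Intervention group x demographic population x time) interaction terms will test the secondary study aim".

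Non-inferiority design states the decision rule for the FEIS (the family caregiver interview on perceived quality of care), and it concerns the overall arm effect: "a 99% confidence interval for the slope for the group assignment variable will be constructed", with the lower limit compared with -7.0. No interval, margin or arm contrast is stated for any subgroup, and Power analyses covers only the overall comparisons.

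**The concern.** The hypotheses are statements about the arm effect inside a subgroup. The named test is a statement about how far the arm effect differs between subgroups. These are different estimands, and no sample size turns one into the other.

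Finding disparities is one of the trial's two aims. If the interaction were the only evidence produced, the trial could reach the end with no result bearing directly on whether telemental health is acceptably close to in-person care for a given racial, ethnic, language or disability group, or on whether rural families rate it better. The risk of overlooking a real deficit is greatest in the smallest groups.

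**Working it through.** **Step 1. What the interaction can and cannot show.** Write D(s) for the telemental minus in-person difference in FEIS change in subgroup s. The interaction estimates D(s) - D(rest).

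- Non-inferiority in s requires D(s) > -7. If D is -9 in every subgroup, the true interaction is -9 - (-9) = 0. The test is then non-significant 99% of the time at two-sided 0.01, although every subgroup is beyond the margin.
- Rural benefit requires D(rural) > 0. Effects of 0 rural and -7 elsewhere give 0 - (-7) = 7. Effects of +7 rural and 0 elsewhere give 7 - 0 = 7. The interaction is identical, and only the second case is a rural benefit.

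This step needs no figure from the plan.

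**Step 2. Inputs for an illustration.**

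- SD: Non-inferiority design gives "A 7-point change in the total FEIS score, which is equivalent to a standardized delta of 0.5", so SD = 7 / 0.5 = 14.
- Size: 500 randomized 1:1 (Abstract, Methods), so 250 per arm.
- Critical value: 2.576, matching the 99% interval (two-sided 0.01).
- Assumed, not in the documents: the subgroup shares, SD 14 in every subgroup, no dropout, no allowance for site clustering.

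The plan has no subgroup power figure to reproduce. Its FEIS requirement of 128 per group is not used here. SD 14, two-sided 0.008 and 80% power give 98 per arm (100 by t-test). An SD of about 16 would give 128, since 98 × (16/14)² = 128, and would make the results below less favourable.

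**Step 3. Formulas.** With n per arm in the subgroup and m = 250 - n per arm in the rest:

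- SE within the subgroup = 14 × √(2/n); 99% half-width = 2.576 × SE
- SE of the interaction = 14 × √(2/n + 2/m)
- P(interaction non-significant when D(s) = -7 and D(rest) = 0) ≈ Φ(2.576 - 7/SE of the interaction)
- Power for subgroup non-inferiority when D(s) = 0: Φ(7/SE within - 2.576)

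**Step 4. Worked case, 20% share (n = 50, m = 200).** SE within = 14 × √0.04 = 2.80; half-width = 7.21. Power for non-inferiority = Φ(2.50 - 2.576) = 0.47. SE of the interaction = 14 × √0.05 = 3.13. P(non-significant) = Φ(2.576 - 2.236) = 0.63.

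| Share | n per arm | SE within | 99% half-width | SE interaction | P(interaction non-significant, deficit 7) | Non-inferiority power, true difference 0 |
|---|---|---|---|---|---|---|
| 10% | 25 | 3.96 | 10.2 | 4.17 | 0.82 | 0.21 |
| 20% | 50 | 2.80 | 7.2 | 3.13 | 0.63 | 0.47 |
| 30% | 75 | 2.29 | 5.9 | 2.73 | 0.51 | 0.69 |
| 50% | 125 | 1.77 | 4.6 | 2.50 | 0.41 | 0.92 |

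The last column is also the power of a within-rural test against zero if the true rural gain is 7 points.

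**Step 5. Would the overall test catch such a deficit?** With a 20% subgroup at -7 and the rest at 0, the overall effect is 0.20 × (-7) = -1.4. The overall SE is 14 × √(2/250) = 1.25 and the half-width 3.2, so the expected lower limit is about -1.4 - 3.2 = -4.6, which clears -7.

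**The case against.** The strongest reply is that the aim is worded as heterogeneity, and an interaction is the proper test of heterogeneity. That stands. A reader might infer that the secondary aim itself is a claim of non-inferiority within each subgroup. The aim sentence does not say so; the mismatch is with the hypotheses beneath it and the conclusion attached to them.

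A reader might also infer that the trial will treat a non-significant interaction as proof of equity. No section says that. The sentence about equitable effects follows the hypotheses and is not tied to a null interaction. What can be said is narrower: the only test named for this aim would not support that sentence.

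A third reply is that subgroup contrasts come from the same fitted model and may be defined in an analysis plan that is not shown. That is possible, and it is why the repair is cheap. But the article does not leave the test open: it names the interaction.

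A fourth is that a uniform deficit beyond the margin should fail the overall non-inferiority test. That is fair for the uniform case in Step 1. It does not cover a deficit confined to one subgroup (Step 5).

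Finally, the figures rest on assumed shares, and larger subgroups do much better. Nor is non-inferiority out of reach at a 20% share: the half-width of 7.21 exceeds the margin only slightly, so an observed difference above +0.21 would clear it.

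**Conclusion.** The point holds in limited form. The interaction is suitable for the heterogeneity aim but cannot, alone, establish non-inferiority across groups or better perceived quality of care among rural participants. That part is logical and holds at any sample size, SD or subgroup share. The rural hypothesis is confined to perceived quality of care, so nothing here concerns rural superiority on other outcomes.

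The size is illustrative only. Under the Step 2 assumptions, the chance that the interaction misses a full-margin deficit falls from 0.82 to 0.41 as the share rises from 10% to 50%, while power for within-subgroup non-inferiority rises from 0.21 to 0.92. Dropout, clustering or a larger SD would worsen both. The primary comparison is unaffected. The change should be made because a stated conclusion of the trial depends on it.

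**What to change.** - For each prespecified subgroup, report the telemental minus in-person difference from the same mixed model, with its confidence interval, against the stated margin where one exists (for the FEIS, the 99% interval against -7).
- Claim subgroup non-inferiority only where the limit clears the margin; otherwise report that subgroup as inconclusive.
- Test the rural hypothesis as the arm contrast in perceived quality of care among rural participants, against zero.
- Keep the three-way interaction as the test of heterogeneity only, and state that a non-significant result is not evidence of equal effects.

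The cost is some analysis-plan wording and one subgroup table, with no new data or participants. The downside is that smaller subgroups will often be reported as inconclusive. At SD 14 and a true difference of zero, 80% power in one subgroup needs 94 per arm: 2 × (14/7)² × (2.576 + 0.842)² = 93.5. That is 188 of the 500 participants, a share of about 38%.

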### Power analyses

Using data from Kalb et al. 2019 [21], we calculated the sample sizes needed to have 80% statistical power to detect the above-mentioned non-inferiority margins with α set at 0.008. For changes in total FEIS scores from baseline to follow-up between the study arms, this study requires N = 128 per group. For a 38% reduction in the probability of a START crisis contact between conditions, this study requires N = 250 per condition. For changes in the mean Aberrant Behavior Checklist irritability scores, this study requires N = 100 per condition.

## Discussion

To our knowledge, this will be the first trial of an established program to provide telemental health crisis services for the IDD population. The study will be executed by an interdisciplinary team of experts that includes stakeholder partners with lived IDD-MH experience. Understanding the benefits of specific telemental health methods has important implications to the design of interventions, within and outside of START. This telemental health study also offers promise to address disparities in access to mental health care for people with IDD across diverse racial, ethnic, cultural, and linguistic groups.

### Responding to cultural context

It is important to recognize that all research is conducted in a cultural context. This includes the question or focus of the research, the research participants and the communities in which they live, the research institution/organization, and the research team. Addressing the cultural context requires a fundamental change in how research is designed, conducted, translated, and disseminated in partnership with diverse stakeholders in general, and for this study, persons with IDD-MH experience in particular.

Persons and their families who are enrolled in START are members of diverse racial, ethnic, cultural, and linguistic groups who reside in varied geographic locales throughout the US. Our study is employing principles and practices of cultural and linguistic competence in order to be responsive of their diverse needs and identities [33, 34]. For instance, the study team: (1) pre-specified facilitators and barriers that have cultural implications (e.g., race, ethnicity, languages spoken, and other cultural factors); (2) acknowledged the diversity across populations by disaggregating data according to race, ethnicity, language spoken, level of intellectual disability, and other cultural factors; (3) employed inclusive practices in study design and reporting; and (4) will analyze heterogeneity in treatment responses and outcomes across prespecified racial, ethnic, linguistic, and cultural groups.

### Advisory council and engagement team

Partnerships with stakeholders at all phases of the research process enhances our study in many ways. First, designing study materials in collaboration with stakeholders, such as plain language informed consent videos, FAQs about the study, and recruitment flyers helps to ensure people with IDD and family members can make an informed decision about their participation. Designing accessible materials can empower people with IDD as well as guardians with diverse educational levels, literacy, or familiarity with research to make an informed choice about participating in this study. Second, clear understanding about the research study during the enrollment process can enhance retention for the duration of the study. Retention is a crucial aspect of this study design, and traditionally can be challenging in long-term studies, or studies with populations at high risk of crisis such as START users. Third, partnership from the ground up with the community means the proposed interventions and outcomes examined are more likely to be relevant for ‘real-life’ service users, including people with IDD enrolled in START and their families, as well as START providers. Insights shared along the way ensure we are measuring outcomes that matter most to people, and the interventions and tools used to reach those outcomes are more likely to be acceptable and adopted in future practice.

In summary, this study seeks to understand the efficacy of telemental health delivery for crisis intervention and prevention services for persons with IDD. While some services and treatments may not require extensive attention to the method of delivery, for people with disabilities this is likely not the case. If our results support including non-inferiority of telemental health to in-person START, these findings will increase the confidence in telemental health service delivery to persons with IDD. It will also increase the prospect of making telehealth more accessible to a wider population of service users. The impact of such would be far-reaching, and enable families who encounter barriers to receiving in-person services to access evidence-based intervention.

## Data Availability

Voluntary, informed, written consent will be obtained during recruitment for the publication of the dataset. The appropriately de-identified study materials and data will be made available publicly available upon completion of the trial. This includes individual-level study data from the final trial dataset, data dictionaries, statistical code, CONSORT (Consolidated Standards of Reporting Trials) diagram (e.g., flow charts), data forms (where appropriate), analytic plan, and study protocols. These data will be available in perpetuity by 2026. These data will be made freely available here: https://www.icpsr.umich.edu/web/pages/pcodr/.

## Abbreviations

IDD: Intellectual/developmental disabilities
START: Systemic, Therapeutic, Assessment, Resources, and Treatment
AC: Advisory Council
CSCPIP: Cross-Systems Crisis Prevention and Intervention Plan
SIRS: START Information Reporting System
FEIS: Family Experiences Interview Schedule
PEIS: Person Experienced Interview Schedule
NI: Non-inferiority
ITT: intention-to- treat
PP: per protocol
CONSORT: Consolidated Standards of Reporting Trials
DSMB: Data Safety and Monitoring Board
PCORI: Patient Centered Outcome Research Institute
